#### Treatment of the aorta

An additional hemodynamically significant stenosis in the aorta must be treated by either PTA or PTA and balloon-expandable uncovered stent placement. For the endovascular treatment of the aorta, as far as we know, there is no evidence, which supports direct stenting. Therefore, we consider PTA, with stenting only on indication, the standard treatment. The PTA balloon and stent should be 1mm oversized.

#### Treatment of the external iliac artery

An additional hemodynamically significant stenosis or occlusion in the external iliac artery must be treated by either remote endarterectomy, PTA or PTA and self-expandable uncovered stent placement. We believe that for the EIA self-expandable stents are more appropriate, due to the tortuosity of the artery and its movement during flexion of the hip. As for the aorta, for the EIA there is also no evidence as far as we know, which supports direct stenting. Of course, since these two types of stents have a very different biomechanical behaviour, evidence on the use of balloon-expandable stents should not be extrapolated to self-expanding stents. The PTA balloon and stent should be 1mm oversized. After recanalization of an occluded external iliac artery PTA and additional self-expandable uncovered stent placement is warranted.

#### Treatment of the common femoral artery

A hemodynamically significant stenosis or occlusion of the common femoral artery must be treated by endarterectomy. This procedure will be combined with treatment of the common iliac artery and, if indicated, external iliac artery. If there is no appropriate outflow from either the superficial or deep femoral artery, the physician may choose to obtain sufficient outflow by using remote endarterectomy, recanalisation with or without stent placement, or bypass.

#### Medication

All patients receive Aspirin 100mg daily and Simvastatin 40mg daily, indefinitely, starting at least one day prior to the procedure. During the intervention all patients receive 5,000 units of Heparin. After the intervention all patients receive Clopidogrel 75mg daily for a period of 4 weeks.

### Investigational product

#### Name and description of investigational product

The Advanta V12 stent (Atrium Medical Inc., Hudson, NH, USA) is a balloon-expandable stainless steel stent that is fully encapsulated in two layers of PTFE. The PTFE has a porosity of 100 to 120 μm. The Advanta V12 covered stent is available in diameters of 5 to 10 mm. Available stent lengths are 16, 22, 38, and 59 mm. All V12 stents are 0.035-inch guidewire compatible and are pre-mounted on a 7F non-compliant balloon catheter with gold markers embedded at the ends of the balloon. Available catheter lengths are 80 and 120 cm. It is the only balloon-expandable PTFE-covered stent that is registered for use in the iliac artery in Europe.

#### Name and description of control group products

In the control group, several uncovered balloon-expandable stents have been selected to choose from at the physician’s discretion. These stents are currently used in the participating centers.

Omnilink Elite stent (Abbott Laboratories, North Chicago, IL, USA). The Omnilink Elite is a balloon-expandable CoCr (cobalt chromium alloy) stent. It is available in diameters of 4 to 10 mm. Available lengths are 12, 16, 19, 29, 39 and 59 mm. All Omnilink Elite stents are 0.035-inch guidewire compatible and are pre-mounted on a 6F dual layer compliant balloon catheter. Available catheter lengths are 80 and 135 cm. It is registered for use in the iliac artery in Europe.

Dynamic stent (Biotronik, Berlin, Germany). The Dynamic stent is a balloon-expandable stainless steel stent, with the stent struts coated with an amorphous silicon carbide coating. It is available in diameters of 5 to 10 mm. Available lengths are 15, 25, 38 and 56 mm. All Dynamic stents are 0.035-inch guidewire compatible and are pre-mounted on a 6 or 7F compliant balloon catheter. Available catheter lengths are 80 and 130 cm. It is registered for use in the iliac artery in Europe.

Express LD Iliac stent (Boston Scientific, Natick, MA, USA). The Express LD Iliac is a balloon-expandable stainless steel stent. It is available in diameters of 6 to 10 mm. Available lengths are 20, 30, 40 and 60 mm. All Express LD Iliac stents are 0.035-inch guidewire compatible and are pre-mounted on a 6 or 7F compliant balloon catheter. Available catheter lengths are 75 and 135 cm. It is registered for use in the iliac artery in Europe.

Palmaz Genesis stent (Cordis Corporation, Bridgewater, NJ, USA). The Palmaz Genesis is a balloon-expandable stainless steel stent. It is available in diameters of 4 to 10 mm. Available lengths are 12, 15, 18, 19, 24, 25, 29, 39 and 59 and 79 mm. In the participating centers, we only use 24, 39, 59 and 79 in the common iliac artery. All Palmaz Genesis Iliac stents are 0.035-inch guidewire compatible and are pre-mounted on a 6 or 7F compliant balloon catheter. Available catheter lengths are 80 and 135 cm. It is registered for use in the iliac artery in Europe.

Scuba stent (INVATEC S.p.A, Roncadelle, Italy). The Scuba stent is a balloon-expandable CoCr (cobalt chromium alloy) stent. It is available in diameters of 5 to 10 mm. Available lengths are 18, 30, 37, 55 and 75 mm. All Scuba stents are 0.035-inch guidewire compatible and are pre-mounted on a 5F compliant balloon catheter. Available catheter lengths are 80 and 130 cm. It is registered for use in the iliac artery in Europe.

### Endpoints/parameters

Definitions of endpoints and parameters are in concordance with the proposed definitions by the DEFINE group, a multidisciplinary team from various specialties involved in PAOD therapies, from Europe and the USA, which has made a case for more standardized reporting in studies for endovascular treatment of PAOD [55,56].

#### Primary endpoint

• Absence of binary restenosis rate. Defined as the percentage of limbs with absence of hemodynamically significant obstruction in the target-lesion after endovascular treatment.

#### Secondary endpoints

• Reocclusion rate. Defined as complete occlusion of the initially treated target-lesion.

• Target-lesion revascularization (TLR) rate. Defined as the rate and frequency of the need for repeated procedures (endovascular or open surgical) due to a problem arising from the target-lesion (+1 cm proximally and distally to include edge phenomena) in surviving patients with preserved limb.

• Immediate outcome:

– Procedural success. Defined as the combination of technical success, device success and absence of procedural complications.

– Technical success. Defined as successful vascular access and completion of the endovascular procedure and immediate morphological success with less than 30% residual diameter reduction of the treated lesion on completion and a systolic pressure gradient of less than 5 mmHg.

– Device success. Defined as exact deployment of the device, according to the instructions for use, using the assigned device only.

• Clinical outcome:

– Distribution of Rutherford stages during follow-up as compared to baseline.

– Functional outcome:

▪ In patients with IC: Improvement in claudication onset time (COT) and absolute claudicating time (ACT) on standardized treadmill test.

– Improvement in disease-related health status, functioning and quality of life. As defined by the Walking Impairment Questionnaire (WIQ) and RAND-36 questionnaire.

• Hemodynamic outcome:

– Mean and median ABI during follow-up as compared to baseline.

• Morphological outcome:

– Acute diameter gain (change in minimal luminal diameter from base-line to post-intervention.

• Target-extremity revascularization (TER) rate. Defined as the rate and frequency of the need for repeated procedures (endovascular or open surgical) due to a problem arising remote from the target-lesion in surviving patients with preserved limb.

• Mortality rate. Mortality rate associated with the endovascular procedure (that is, mortality within 30 days post-procedure or mortality during a hospitalization >30 days due to the procedure) will be reported separately, as well as overall mortality.

• Complication rate. In contrast with AE’s and SAE’s, which do not need to be related to the treatment, only complications that are (likely) related to the treatment will be reported. This is at the discretion of the investigator.

– Complications will be scored as ‘major’ or minor’. A major complication is a complication that:

▪ Leads to death;

▪ Results in a life-threatening illness or injury;

▪ Results in permanent impairment of a body structure or bodily function;

▪ Requires inpatient hospitalization or prolongation of existing hospitalization;

▪ Results in medical or surgical intervention to prevent permanent impairment to body structure or bodily function.

– Complications will be classified in to four complication categories:

▪ Access site complication (access site including distal to the site): Hematoma/bleeding, arterial/venous occlusion/thrombosis, severe vasospasm, intimal injury/dissection, pseudoaneurysm, arteriovenous fistula, vascular perforation or rupture, arterial embolization distal to puncture site.

▪ Treatment site complication (treatment site including distal to the site): Hematoma/bleeding, arterial/venous occlusion/thrombosis, severe vasospasm, intimal injury/dissection, pseudoaneurysm, arteriovenous fistula, vascular perforation or rupture, arterial embolization distal to treatment site.

▪ Organ-specific complication:

∘ Neurological: TIA, minor and major stroke, seizure;

∘ Cardiovascular: Hypotension or hypertension requiring treatment, arrhythmia requiring treatment, myocardial ischemia/infarction, chronic heart failure;

∘ Respiratory: Profound hypoxia, pulmonary edema, respiratory arrest, pulmonary embolism, pneumothorax;

∘ Gastrointestinal: Gastric bleeding, pancreatitis, peritonitis, abscess, perforation of hollow viscus.

▪ Systemic complication: Allergic/anaphylactic reaction, renal failure, idiosyncratic reaction to drug, fluid/electrolyte imbalance.

• Amputation rate. Divided in to minor (below the ankle) and major (above the ankle). Major amputation is sub-divided in to below-the-knee and above-the-knee. Planned and unplanned amputations will be reported separately. Planned amputations are defined as amputations that were planned prior to the revascularization procedure, that is, when the revascularization procedure is performed to improve the vascularization (and thereby healing potential) of the planned amputation wound.

• Rate of device-specific problems, for example, stent fracture, stent migration.

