### Follow-up of subjects withdrawn from treatment

Patients that for whatever reason receive a different treatment than randomized, or received no treatment will be followed-up and included in the trial, based on intention-to-treat. Patients that are withdrawn from follow-up will be considered lost to follow-up.

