#### Actuarial analysis

Absence of binary restenosis rate and reocclusion rate will be calculated with actuarial (life-table) analysis and will be expressed as a percentage with a standard error and 95% CIs. Logrank tests will be used to determine if differences between the estimates are significant. For these endpoints, we will also calculate a combined endpoint with survival, for example, binary restenosis-free survival etc. Based on the literature, we expect that mortality will be negligible and will not influence the results, and these separate analyses will be performed to check this assumption.

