#### Univariate analysis

Univariate analysis will be performed to assess differences in the other aforementioned primary and secondary endpoints.

Continuous data: Averages with standard deviation (parametric data) or medians with percentiles (non-parametric data) will be calculated. Differences between both groups will be tested using a Student’s *t*-test (parametric data) or a Mann–Whitney *U*-test (non-parametric data). Differences with a *P*-value <0.05 will be considered statistically significant. The following endpoints will be assessed:

Post-intervention COT and ACT;

Mean ABI.

Categorical data: Frequencies will be calculated and difference between both groups will be tested using Chi-squared test. Differences with a *P*-value <0.05 will be considered statistically significant. The following secondary endpoints will be assessed:

• Target lesion revascularization rate and target extremity revascularization rate;

• Procedural, technical and device success rate;

Mortality rate, complication rate, amputation rate;

• Rate of device-specific problems.

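### TLR and TER are confined to survivors with a preserved limb and compared by chi-squared; definition and test do not fit together under either reading

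*Protocol article*

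**What the plan says.** Under Secondary endpoints, the TLR definition covers how often repeat procedures on the target lesion are needed, and its closing words are "include edge phenomena) in surviving patients with preserved limb". The TER definition has the same limit: "due to a problem arising remote from the target-lesion in surviving patients with preserved limb".

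Under Univariate analysis, the rule for categorical data is "Frequencies will be calculated and difference between both groups will be tested using Chi-squared test", and the first item on the list it governs is "Target lesion revascularization rate and target extremity revascularization rate". Mortality and amputation are on that list as separate endpoints.

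Under Actuarial analysis, time-based methods go to two other endpoints: "Absence of binary restenosis rate and reocclusion rate will be calculated with actuarial (life-table) analysis", with log-rank tests. The check on mortality is confined to the same two: "For these endpoints, we will also calculate a combined endpoint with survival".

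The sections on withdrawal keep withdrawn or differently treated patients in the analysis by intention-to-treat. They do not say how deaths, amputations or losses enter the TLR or TER denominator.

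**The concern.** Whether a patient survives and keeps the limb is known only after randomisation and may depend on the stent. The trial admits patients with critical limb ischemia and counts major amputation as an endpoint, so limb loss is a foreseeable outcome here.

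If the restriction selects the analysis set, the TLR comparison is made in subgroups chosen by outcome, and a stent that failed, was re-treated and was followed by limb loss leaves both numerator and denominator. The protection that randomisation gives is then lost for that endpoint.

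A second issue is the test. The definition speaks of how often procedures recur, but a two-by-two table records only whether a patient ever had one. It uses neither the time of the procedure nor incomplete follow-up. Reocclusion, an event in the same lesion over the same two years, is analysed with methods that do use time, so the two results will not be directly comparable.

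**Working it through.** **The plan's own figures.** The document gives no expected rate or size for TLR or TER. Its only calculation is for the primary endpoint (Sample size calculation: 90% v 72% free of restenosis at 2 years, 79 per group, 87 after losses). It reproduces:

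- Hazard ratio = ln(0.90)/ln(0.72) = 0.321.
- Freedman's log-rank formula, two-sided 0.05, 80% power: 30 events.
- Mean event probability = 1 − (0.90 + 0.72)/2 = 0.19; 30/0.19 = 157.9 patients, or 79 per group.
- 79/87 = 90.8% retained, so planned loss is about 9.2%.

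Nothing in that calculation is disturbed by this point. It supplies only an arm size and stand-in failure rates for the illustrations.

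**The two readings set against the test.**

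- Analysis population: patients who die or lose the limb are removed, with any earlier TLR. The test is computable, but not on the randomised groups.
- Time at risk: a procedure counts if done while the patient is alive with the limb. A re-treated patient who is later amputated still counts. Patients who die or lose the limb before any procedure then have incomplete risk time, which a table of frequencies cannot represent.

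**Illustration 1 (first reading).** Restenosis planning rates stand in for TLR: 0.28 × 87 ≈ 24 uncovered and 0.10 × 87 ≈ 9 covered. Let *a* and *b* be the assumed proportions of re-treated and other patients who die or lose the limb. Neither is in the document.

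Rate among survivors with limb = T(1 − a) / [T(1 − a) + (87 − T)(1 − b)]

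- No exclusions: 24/87 = 27.6% v 9/87 = 10.3%; gap 17.2 points.
- a = 20%, b = 5%: 19.2/(19.2 + 59.85) = 24.3% v 7.2/(7.2 + 74.1) = 8.9%; gap 15.4. TLR patients removed: 4.8 + 1.8 = 6.6 of 33. All patients removed: 7.95 + 5.7 = 13.65 of 174 (7.8%).
- a = 5%, b = 2%: 22.8/84.54 = 27.0% v 8.55/84.99 = 10.1%; gap 16.9.
- a = b: the rates and the gap do not change.

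**Illustration 2 (direction).** Assume true TLR of 10% v 20%, a fraction *l* of the arm excluded, and a share *f* of those excluded having had TLR. Observed rate = (p − f·l)/(1 − l).

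- l = 2% in both arms: gap 0.10/0.98 = 10.2 points for any common f.
- l = 5% v 10%, f = 1: 5.3% v 11.1%; gap 5.8.
- l = 5% v 10%, f = 0.5: 7.9% v 16.7%; gap 8.8.
- l = 5% v 10%, f = 0: 10.5% v 22.2%; gap 11.7.
- l = 5% v 15%: gap 0.6 with f = 1 and 13.0 with f = 0.

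The gap can therefore shrink or widen, and it barely moves when exclusions are few and balanced.

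**The case against.** The wording does not say alive with the limb at 24 months, so the at-risk reading is open, and on it a patient re-treated before amputation is still counted. The definitions are declared to follow a published reporting standard. Mortality and amputation are reported separately, and in-stent stenosis or occlusion must be documented, so a failure identified before death or limb loss still reaches the restenosis and reocclusion analyses. Everyone has the same planned two years, mortality is expected to be negligible, and a proportion at a fixed horizon is less efficient rather than wrong. All of this limits the severity. It does not rescue the pairing of definition and test, because the at-risk reading is the one that chi-squared cannot serve. A reporting definition also does not dictate a test.

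Stronger readings are tempting but not supported:

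- **That the restriction contradicts intention-to-treat.** The rule that patients who "received no treatment will be followed-up and included in the trial, based on intention-to-treat" concerns treatment received, and its companion section concerns withdrawal. Neither sets a TLR denominator. There is tension with the principle, not a textual contradiction.
- **That the worst failures certainly vanish, biasing TLR downwards.** This needs the first reading and attrition figures that the document does not give. Deaths need not be stent failures, and Illustration 2 shows that the gap can widen.
- **That chi-squared overstates significance for mortality, amputation and device problems.** For 4 v 0 of 87 the P value is 0.043 uncorrected, 0.129 with continuity correction and 0.121 by Fisher's exact test. The protocol does not say which chi-squared it means, and a small-cell fallback is ordinary SAP detail. It forms no part of this point.

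**Conclusion.** The point holds for the definition and test as paired. TLR and TER are tied to post-randomisation outcomes and given a test that either compares non-randomised subsets or cannot handle the risk time that the definition implies. That test also leaves out timing and repeat procedures and has no means of using partial follow-up, with loss planned at just under 10%. The survival-combined check covers restenosis and reocclusion only, and does not address limb loss.

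The size of any bias is not determinable from the document. Under assumed attrition it runs from negligible to several points: 17.2 to 15.4 with 20% v 5%, and 17.2 to 16.9 with 5% v 2%. The more extreme, unbalanced exclusions of Illustration 2 turn a true 10-point gap into anything from 0.6 to 13.0 points. These figures rest on assumed rates throughout and, in Illustration 1, on restenosis rates standing in for TLR. Only secondary endpoints are affected; the primary analysis and the sample size are not.

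**What to change.** - Analyse TLR and TER as time to first procedure in all randomised index limbs, with death and major amputation as competing events. Estimate by cumulative incidence and compare by cause-specific log-rank test, in line with reocclusion.
- Report repeat procedures descriptively, per limb-year.
- Show the rate under the cited reporting definition alongside, and state whether its restriction means status at the end of follow-up or time at risk.

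The cost is a change of wording and slightly more analysis. Dates of re-intervention, major amputation, death and last contact must be recorded. The follow-up parameters list amputation and mortality without mentioning dates, and the restenosis parameters list no re-intervention date, so it should not be assumed that these are already captured. The main rates will differ somewhat from the cited definition, which is why both should be shown.
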